## Methods

### Study Design

This will be a 3-part study that includes focus groups and cognitive interviews to develop an eHealth intervention for HIV-positive and HIV-negative black and Hispanic MSM, and a small randomized controlled trial (RCT) to evaluate that intervention. In phase 1, we will use 4 to 6 focus groups of 5 to 8 participants each to learn about TasP, PrEP, and social media use in the target population, as well as obtaining feedback on an existing interactive website (Men2MenRI [33]). Members of our team previously developed the website targeting white MSM in Rhode Island. Phase 2 will use cognitive interviews with 8 participants and an open pilot with 16 participants to develop and assess the acceptability of IMB- and SCT-grounded social media message content designed to motivate and encourage access to our newly developed website. In phase 3, we will conduct a small RCT (n=100 participants, with 50 in each arm) comparing the combination of sending social media messages plus the website (active arm) versus the website alone (control arm). Study materials (eg, recruitment flyers, interview guides, questionnaires, website, and social media messages) and findings (eg, qualitative and quantitative data) will also be assessed by a community advisory board made up of 6 to 12 members from the local community who reflect the target groups. The study is approved by the Brown University Institutional Review Board (#1612001661), Providence, Rhode Island, USA, and the US National Center for HIV/AIDS, Viral Hepatitis, STD, and TB Prevention’s project determination process. This study is also registered on ClinicalTrials.gov (NCT03404531).

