### Participant Recruitment

Participants will be HIV-positive and HIV-negative black and Hispanic MSM who are 18 years of age and older living or working in the Providence Metropolitan Area (all of Rhode Island and Bristol County, Massachusetts). Participants must also fit the CDC definition of high risk—that is, have engaged in condomless anal intercourse within the past 6 months; be biologically male and identify as male; and be able to give written informed consent in English or Spanish. For phase 3, participants must also report not taking PrEP if they are HIV-negative, or in HIV care or taking treatment if they are HIV-positive, at the time of enrollment in the study. We will recruit participants for all phases of the study using a variety of methods, including advertisements online and on public transportation; posted signs and flyers in local community and commercial venues; and in-person outreach at places where the target population congregates, such as community-based organizations, clinics, bars, and clubs. Individuals interested in participating will be screened for eligibility over the phone using the aforementioned criteria. Participants will provide written informed consent prior to participating in the focus group, cognitive interview, or baseline assessment.

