### Measures

Phases 1 and 2 measures will involve using qualitative interview guides, informed by the extant literature and developed by the team, to identify important themes in the data. For phase 3, participants will complete the study assessment at enrollment (baseline) and at a 6-month follow-up, which will be digitally administered using iPads. The assessment will include self-report questions about HIV testing history, date(s) of previous testing, source(s) of previous testing, viral load, CD4 count, linkage and retention in care, TasP uptake, HIV medication, adherence and viral load if HIV-positive, and consideration of PrEP, including barriers and facilitators and its uptake, if HIV-negative. The assessment will also include measures that we will develop from the focus group data to assess participants’ knowledge, attitudes, and behavioral intentions toward TasP and PrEP use. Validated measures will include event-level characteristics of sexual risk episodes over the past 3 months, using the timeline follow-back interview method, with information on sexual activities, relationship with partner(s), partner gender, use of alcohol or drugs prior to or during, and use of condoms for each episode. Phase 3 will also involve fidelity monitoring of participants’ use of the intervention, including information about when they check or receive messages, whether they reply to messages or input information via messages, and whether they log calls to study staff.

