### Study Outcomes

The primary outcome of the study will be levels of and increases in TasP or PrEP uptake in the intervention group compared with the control group, as determined by using assessment data from phase 3. Secondary outcomes include increases in levels of TasP- and PrEP-specific knowledge, favorable attitudes, and behavioral intentions regarding TasP and PrEP among participants in the intervention group. Lastly, we will explore decreases in sexual risk behaviors in the intervention group relative to the control.

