### Planned Analyses

For the qualitative analyses in phases 1 and 2, we will independently read and code professional transcriptions of the focus groups and interviews, and will convene regularly to discuss emerging themes and systematically establish categories. Finalized thematic codes will provide an exhaustive categorization tool of concepts and themes described by participants. Multiple coders will analyze subsets of data, interrater reliability will be assessed, and any discrepancies will be resolved with discussion.

In phase 3, we will first assess the randomization process by comparing baseline demographic variables of participants in each arm; we will incorporate any variable for which randomization did not result in equal proportions in each arm into the multivariate models as a potential confounding variable. Next, we will conduct primary inferential analyses to test our primary hypothesis (ie, that messages sent over social media will increase TasP and PrEP uptake among the men in the intervention arm versus the control arm) followed by our secondary (increases in knowledge of, more favorable attitudes toward, and behavioral intentions regarding TasP and PrEP use between men in the intervention and control arms) and exploratory (decrease in sexual risk behaviors among men in the intervention arm in comparison with the control arm) hypotheses. Since the primary and tertiary outcome measures are binary, we will first compare proportions by randomization arm separately for each measurement period using standard bivariate analytic techniques (eg, Spearman rank-order correlations, odds ratios, and Fisher exact test). We will use ordinary least squares regression on our secondary measures of knowledge, attitudes, and behavioral intentions, which we will assess using continuous scales. We will contrast outcomes in the intervention versus comparison groups over time via generalized linear mixed models. Given the binary nature of our TasP and PrEP uptake and sexual risk measures, we will specify a logit link function for our generalized linear mixed models.

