We will follow an intent-to-treat design and will include data from all enrolled participants in the analysis, regardless of level of intervention use. We will compare characteristics of participants who are lost to follow-up with those who are evaluated to assess for systematic patterns that could influence results. Following intent-to-treat principles, we will include all randomly assigned participants in the data analyses.

Effect-size estimates determined through the small RCT will be essential in the design of a larger and fully powered efficacy study that tests intervention effects on TasP and PrEP uptake and behavioral risk reduction. We are well aware of the limitations of relying exclusively on small-scale pilots to determine whether novel intervention approaches are promising, namely that sizable standard errors are associated with effect sizes due to the small sample size. However, we are primarily interested in exploring the pattern of results for any evidence of support for the intervention's influence on the primary and secondary outcomes. Our proposed sample size of 100 will be sufficient to detect an effect size of 0.3 or greater between the 2 groups, with 80% power and a 2-tailed alpha level of .05. Furthermore, we will be able to detect similar effect sizes (of ≥0.3) with respect to condomless anal intercourse and secondary analysis of social-cognitive behaviors.

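### Sexual risk is recorded episode by episode but analysed as binary; a baseline-adjusted count of condomless acts would be a cheap, more sensitive exploratory outcome

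*Protocol article*

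**What the plan says.** - **Measures** (Protocol article): Phase 3 collects "event-level characteristics of sexual risk episodes over the past 3 months, using the timeline follow-back interview method", and the details recorded include "use of condoms for each episode". A count of condomless anal acts per man can therefore be derived at baseline and at 6 months.
- **Participant Recruitment**: to be eligible, men must "have engaged in condomless anal intercourse within the past 6 months".
- **Study Outcomes**: the aim for this outcome is directional: "we will explore decreases in sexual risk behaviors in the intervention group relative to the control". It ranks below the primary and secondary outcomes.
- **Planned Analyses**: "Since the primary and tertiary outcome measures are binary, we will first compare proportions by randomization arm separately for each measurement period", with Fisher's exact test and odds ratios among the methods listed. For the mixed models, "Given the binary nature of our TasP and PrEP uptake and sexual risk measures, we will specify a logit link function".
- **Planned Analyses**, on sample size: 100 participants are said to be "sufficient to detect an effect size of 0.3 or greater between the 2 groups" with 80% power at two-sided 0.05. Similar detectable effects are claimed for condomless anal intercourse. Neither the effect-size metric nor an expected rate is given.

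**The concern.** The measures are not binary by nature. The instrument yields a count, and the plan chooses to dichotomise it. This is a stated analysis choice, not a detail left to a later document.

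The choice fits the hypothesis poorly. If the variable is any versus no condomless act in 3 months, a man who goes from ten such acts to three scores the same as a man who does not change. Because everyone enters with recent condomless sex, most men start in the any category, and only complete cessation over the window counts as improvement.

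At stake is the sensitivity of the exploratory comparison and the usefulness of its effect estimate. Planned Analyses wants pilot effect sizes for designing a larger study of uptake and behavioural risk reduction, so an insensitive outcome could be carried forward.

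**Working it through.** **1. The plan's own figure.** The claim is a detectable effect of 0.3 with 50 per arm and 80% power. It depends on the metric.
- Standardised mean difference: n per arm = 2(1.960 + 0.842)²/0.3² = 174.4, so 175. With 50 per arm, power = Φ(0.3/√(2/50) − 1.96) = Φ(1.50 − 1.96) = 32%.
- Phi (w) for a 2×2 table: power at N = 100 is Φ(0.3 × √100 − 1.96) = Φ(1.04) = 85%.

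The figure is reproduced on the second scale and not on the first. In any/none terms, 80% power with 50 per arm needs a fall from 95% to 75%, 90% to 67%, 80% to 53.5%, or 70% to 42.5%.

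**2. Any/none against count, worked by hand.** Assume negative binomial counts with control mean μ = 4 acts per 3 months and dispersion k = 1, 50 per arm, no baseline adjustment.
- P(any) = 1 − (k/(k+μ))^k. Control: 1 − 1/5 = 0.80. Acts halved (mean 2): 1 − 1/3 = 0.667.
- Power on any/none: the pooled SE is √(2 × 0.7333 × 0.2667/50) = 0.0884 and the unpooled SE is √((0.16 + 0.2222)/50) = 0.0874. Then Φ((0.1333 − 1.96 × 0.0884)/0.0874) = Φ(−0.458) = 32%.
- Power on the count: SE(log rate ratio) = √[((1/4 + 1) + (1/2 + 1))/50] = 0.2345. Then Φ(0.693/0.2345 − 1.96) = Φ(0.996) = 84%.
- Rate ratio 0.7 (mean 2.8): any falls only to 0.737, with 11% power. On the count, SE = √[(1.25 + 1.357)/50] = 0.228 and power = Φ(0.357/0.228 − 1.96) = 34–35%.

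Over assumed means of 4, 8 and 12 and k of 0.5, 1 and 2 (Mann–Whitney from 3,000 simulations per setting):

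| Rate ratio | Any/none | Negative binomial | Mann–Whitney |
|---|---|---|---|
| 0.5 | 15–44% | 61–99% | 42–97% |
| 0.7 | 7–14% | 22–63% | 14–53% |

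The count analysis had more power in all 27 scenarios tried (rate ratios 0.5, 0.6 and 0.7).

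**3. Simulation with the entry criterion imposed.** Assumed: Poisson-lognormal counts, mean 2 to 8 acts per 3 months before selection, squared CV 1 to 2, 70% of log-variance stable over time, at least one condomless act in the 6 months before entry, 50 per arm, no dropout.
- Baseline any rate: about 78–96%. Halving acts lowers any by 9–19 percentage points.

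| Rate ratio | Fisher on any/none | ANCOVA on log count, baseline-adjusted |
|---|---|---|
| 0.5 | 18–47% | 71–97% |
| 0.7 | 4–14% | 28–55% |

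- Type I error of the log-count ANCOVA was 4–6%.

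**4. Does adjustment rescue the binary outcome?** In a 400-run simulation (means 4 and 8, acts halved), logistic regression adjusted for baseline any/none had 16–42% power, much like Fisher's test. A robust negative binomial model was also powerful, but its type I error was 6–8%. That favours log-count ANCOVA as the main analysis.

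**The case against.** - **The binary variable is undefined.** A per-episode condom yes/no in a logit mixed model would also be binary and would keep the episode data. This stands as a caveat. The Fisher comparison of proportions by arm makes one value per man likelier, but does not settle it. A per-episode measure would still miss a fall in the number of acts.
- **A reader might infer that any/none sits at a ceiling and hardly moves.** The documents do not support that. Entry uses a 6-month window and the outcome a 3-month window, and no act rate is given. Under the assumptions above, baseline is 78–96% and moves 9–19 points when acts are halved.
- **A reader might blame dichotomising alone for low power.** Fifty per arm is also a cause: a continuous outcome with a standardised difference of 0.3 has only 32% power. Halving acts is a large effect for messages added to a website that both arms receive. At rate ratio 0.7 the count analysis is underpowered too.
- **A reader might infer that the stated power for condomless anal intercourse is simply wrong.** It fails as a standardised mean difference and holds as phi. Since the metric is not named, the text cannot be convicted of either.
- **The outcome is exploratory in a pilot** that admits large standard errors, and no trial decision rests on this test. That limits the weight of the point, not its correctness.

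**Conclusion.** The point holds as a cheap improvement to an exploratory analysis and is minor. The plan collects episode-level data and then specifies a binary analysis that, on its likelier reading, cannot see partial reductions in a sample selected for the behaviour. Under the assumed act rates, using the count raises power from about 18–47% to 71–97% if acts are halved, and from about 4–14% to 28–55% at a rate ratio of 0.7. The ranking was the same in every setting tried. The absolute figures rest on assumed means, dispersion and stability and on no dropout, none of which the protocol states. The primary and secondary outcomes are not affected.

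**What to change.** In Planned Analyses:
1. Define the exploratory sexual-risk outcome as the number of condomless anal acts in the 3 months before the 6-month visit.
2. Analyse it by ANCOVA on log(count+1) with robust standard errors, on arm, baseline log(count+1), HIV serostatus and race/ethnicity (the stratification factors).
3. Give a negative binomial rate ratio with the same covariates as a check.
4. Keep any/none, explicitly defined per man, as a descriptive summary by arm and visit.

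**Cost:** analysis wording only; no new data, visits or participants. **Downsides:** the negative binomial rate ratio is sensitive to a few very high counts and its robust test may be slightly anticonservative; the log-count effect is less directly interpretable. Reporting both deals with most of this.

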## Results

Development of this project began in May 2016. Participant recruitment for phase 1 began in August 2017 and is scheduled to be completed in August 2018. Phase 2 recruitment will begin in August 2018 and is scheduled to be completed in August 2019. Phase 3 recruitment will begin in August 2019 and is scheduled to be completed in August 2020.

## Discussion

### Principal Findings

The goal of this project is to add to the science about HIV prevention interventions and eHealth among black and Hispanic MSM in the United States. Successful interventions are urgently needed to reduce the burden of HIV for racial and sexual minority men. If the intervention is effective, social media messaging and culturally tailored online information could be a low-cost, high-impact way to increase uptake of HIV prevention methods in these high-risk populations. This study will also generate much-needed data on social media’s utility for eHealth interventions among HIV-positive and HIV-negative black and Hispanic MSM. While eHealth has substantial potential, it remains hard to assess its ability to motivate behavioral change given the lack of data available, particularly for racial and ethnic minority MSM.

### Study Limitations

There are study limitations that are important to highlight. First, given that this study will focus on HIV-positive and HIV-negative black and Hispanic MSM living in the Providence Metropolitan Area, our findings may not generalize to similar men living in other areas of the United States. Second, our results will be based on data that are self-reported by participants, which is subject to recall and social desirability biases. Third, the website and social media messages that we will develop, based on feedback from the focus groups and cognitive interviews, will be limited by the constant evolution of technology and its outpacing of research.

### Study Strengths

Despite these limitations, this study has several strengths. First, it uses a combined approach to TasP and PrEP uptake that leverages advances in social media as a platform for motivating behavioral change to potentially overcome some of the noted barriers to use of HIV treatment and prevention services. Second is the use of social media messages grounded in IMB and SCT to provide targeted groups with timely information and motivational cues to access the website about TasP and PrEP. A third advantage is that the website will be culturally tailored and specifically designed by and for HIV-positive and HIV-negative black and Hispanic MSM. Fourth, findings from this research have the potential to influence policy guidelines and recommendations for TasP and PrEP uptake for high-risk groups.

### Conclusions

Development and evaluation of this newly developed website will allow for improved implementation and delivery of TasP and PrEP, and will help prevent HIV acquisition and transmission among high-risk HIV-positive and HIV-negative black and Hispanic MSM in the United States. We will use the results of this study for a larger-scale trial to test the effectiveness of the combined messages, plus the website, on behaviors leading to HIV treatment and prevention for these 2 populations. In addition, we will conduct future research to examine the long-term effects of the website on TasP and PrEP adherence among their users.

## Abbreviations

CDC: Centers for Disease Control and Prevention
IMB: information-motivation-behavioral skills
MSM: men who have sex with men
PrEP: preexposure prophylaxis
RCT: randomized controlled trial
SCT: social cognitive theory
TasP: treatment as prevention
